**A.4. Interventions to prevent colon cancer.** Numerous randomized controlled trials of lifestyle risk factors for colon cancer prevention have been conducted in recent years, but all have focused on dietary changes or taking supplements with one exception.^45, 90-92^ That study randomized participants to a 12 month moderate to vigorous aerobic exercise program or delayed two-month intervention and examined changes in colon cell architecture and proliferation.^93, 94^ Given the wealth of observational data demonstrating the large risk reductions that can occur with participation in physical activity, it is surprising that more randomized controlled trials of colon cancer prevention have not been conducted.

There is a lack of interdisciplinary research that combines theoretically driven behavior change interventions and etiologically relevant endpoints in a rigorous randomized controlled trial design for colon cancer prevention or risk reduction. This study improves on previous work by measuring PA and biomarkers. The lack of focus in the existing literature on physiologic parameters in physical activity studies, and the lack of quality interdisciplinary research, is a weakness of the existing literature. Our study is innovative and important in its ability address these multiple levels of outcomes.

**A.5.Measuring physical activity.** Despite walking being the most commonly reported physical activity,^23, 24^ recall of walking presents numerous challenges, including recall of occurrences, speed, and/or intensity.^95-97^ Thus, objective measurement tools that can detect gradations in walking behavior are useful physical activity measures.

Pedometers are easy to use, relatively low cost, reliable and accurate.^98^ Pedometers capture the vertical accelerations associated with normal ambulation and thus, measure the total number of steps taken over a given period of time (i.e. day, week). Most studies suggest that pedometers have acceptable validity when compared to more comprehensive objective measurement devices like accelerometers, particularly when measurement is focused on walking behaviors.^99, 100^

The combination of the high frequency of walking as a physical activity and their comparatively low cost makes pedometers well suited for population-based research. In addition, pedometers are non-invasive, low burden tools that are socially acceptable and practical in-vivo measures of physical activity.

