**C.3. Measures**

**C.3.a. Objective physical activity measurement.** Within two weeks of their baseline assessment all participants will come in to complete the consent and be fitted with a blinded pedometer with instructions on placement and wear. Participants will be instructed to wear the device for the 7 days prior to their baseline visit. All pedometers will be blinded to minimize behavior change in response to the assessment. Logs will be collected at the baseline visit. Log data will be used to determine days and hours of wear. At the baseline visit, pedometers will be collected and data will be downloaded to the study computer and processed using manufacturer software. Participants will also be provided with an accelerometer during this period for assessment of total physical activity levels. Participants will also provide objective physical activity data at follow-up as outlined below.

**C.3.a.1 Pedometer.** We will use the Omron HJ 720IT pedometer in this study. This pedometer displays seven days of step count data (when not blinded and sealed), but can store up to 41 days of step count data in the memory for later download. Research has suggested that the Omron pedometer technology may have superior accuracy among elderly and obese individuals.^119, 120^ Given the high prevalence of obesity in the general population^121^ and the age range of our eligibility criteria, we believe it is prudent to use the Omron device. Participants will complete logs and record daily hours of wear.

**C.3.a.2. Accelerometer.** We will use the Actigraph brand accelerometer in this study. The accelerometer will allow us to estimate the participants’ total physical activity level including minutes of moderate or vigorous intensity physical activity as well as a summary indicator of physical activity that accounts for both intensity and duration, expressed as metabolic equivalent (MET) minutes per week. Finally, it will allow us to estimate the participants’ energy expenditure.

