Accelerometers are generally recognized as a “gold-standard” approach for the objective measurement of physical activity. Accelerometers record the g-forces common to movement and translate them into data that reflect the frequency and intensity of movement, sampled at set intervals. With accelerometry the duration time spent at defined intensities of activity can be determined, which allows for the more valid assessment of physical activity. In interventions of physical activity behavior change, accelerometers provide the most valid estimates of change in energy expenditure.

**C.3.b. Physiologic assessment.** At the baseline and follow-up visit, all participants will undergo a fasting blood draw. Staff will also measure participants’ weight and height.

**C.3.b.1. Serum marker measurement.** Blood will be collected after a 12 hour fast. Participants will also be instructed not to consume alcohol for 18 hours prior to the blood draw or take NSAIDs for 24 hours prior to blood draw. Because daily physical activity is part of the intervention message, participants will not be asked to terminate physical activity, but limit it. Specifically, participants will be asked not to participate in vigorous physical activity for 12 hours prior to the blood draw and not to participate in any moderate or vigorous intensity physical activity for three hours prior to the blood draw.

The Center for Clinical Studies (CCS) will oversee the physiologic assessment, including sample collection, processing, and storage. Samples will be processed in order to allow subsequent analysis of levels of insulin, C-peptide, IL-6 and PGE-2. Blood will be processed and stored as serum, EDTA plasma, and red blood cells. Each participant’s baseline and follow-up blood samples will be assayed in the same batch. In addition, an equal number of samples from each study arm will be included in each batch.

**C.3.b.2. Body composition assessment.** Body weight and height will be measured in duplicate using a digital scale and tape measure constructed specifically for research quality measures. We will also measure waist and hip circumference.

**C.3.c. Questionnaire.** Following the physiologic assessment and pedometer return, participants will be provided a questionnaire that includes physical activity, potential confounder and sociodemographic information. Measures are summarized in Table 2 and are described in detail below.

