**C.6. Intervention evaluation and outcome measurement**

**C.6.a. Objective physical activity.** One week prior to the conclusion of the study, participants will come into receive a blinded sealed pedometer to wear for seven days. Participants will again be given an Actigraph device to wear for seven days. At the end of the seven day period, all participants will return to Washington University for their study conclusion evaluation visit. Data from the devices will be processed as at the baseline visit. Participants will complete a questionnaire and undergo a final physiologic examination and blood draw.

**C.6.b. Physiologic measures.** Participants will undergo physiologic measurement identical to baseline at the end of the study. We will measure height and weight, as well as insulin, C-peptide, IL-6 and PGE-2 levels. Blood will be processed and stored as serum, EDTA plasma, and red blood cells.

**C.6.c. Questionnaire.** Following the physiologic assessment and pedometer return, participants will be provided a questionnaire identical to that used at baseline that includes items querying physical activity, potential confounder and sociodemographic information.

**C.7. Incentives.** All study participants will receive $50 each for completing the baseline assessment as well as $50 for attending the 3 month (study end) visit. Participants will also be allowed to keep their study pedometers.

**C.8. Retention strategies.** To ensure high retention rates of study participants, we will employ several strategies including providing detailed information on risks associated with study participation to build trust, accessing participant information through their physician to help reinforce the clinical support for the study program, and the use of incentives. In addition, at enrollment we will collect multiple sources of contact information from participants including home, work and mobile phone numbers as well as email addresses where available. We will also request the name and contact information for a friend or family member who can be contacted in the event the participant relocates. Our regular phone contact will help participants feel connected to and invested in the study.

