**C.11.b. Secondary Aim: To compare changes in the secondary outcome of physical activity over three months.**

Hypothesis 2.1: We will evaluate the intervention effectiveness at changing physical activity levels by comparing change in average step count recorded on blinded pedometers from baseline to follow up between the intervention groups. Mixed effects regression will be used to account for the longitudinal design. The outcome variable will be the average steps per day for the measurement period. The measurement period at baseline and follow-up is the seven day period participants were required to wear the blinded pedometer. Only days where the participant wore the pedometer for at least eight hours will be counted and the average will be based on the number of full days of wear. The analysis is based on change using mixed effects regression models similar to that outlined in Aim 1. We will also examine the percentage of intervention participants meeting the 10,000 and 13,000 steps per day goals at the study conclusion based on data recorded on the pedometer. We will use the last seven days of the phase. We will also examine the percent of participants adhering to their study arm prescription (defined as completing 90% of required physical activity) at three months. We will examine whether sociodemographic factors, overall physical activity level, or family history of colon cancer are associated with meeting the intervention step count requirement. Finally, we will examine whether the intervention changed total physical activity levels by comparing baseline and follow-up total physical activity levels (as measured by the PPAQ) in the intervention groups and by comparing change in those levels between the intervention groups using the general estimating equation modification to linear regression.

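### C.11.b rests the total physical activity comparison on self-report alone, while the accelerometry collected for the same purpose has no stated analysis

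*Protocol*

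**What the plan says.** **Analysis.** C.11.b first compares change in average daily steps on blinded pedometers between arms, using mixed effects regression. It ends with a supplementary analysis of total physical activity, "comparing baseline and follow-up total physical activity levels (as measured by the PPAQ"). That analysis covers both change within the arms and the difference in change between them, using linear regression with generalised estimating equations.

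**Accelerometer.** C.3.a introduces the device with its purpose: "Participants will also be provided with an accelerometer during this period for assessment of total physical activity levels". C.3.a.2 says what it yields: "total physical activity level including minutes of moderate or vigorous intensity physical activity". Energy expenditure and a weekly MET-minute summary are listed there too. The same section calls accelerometers a generally recognised gold-standard "approach for the objective measurement of physical activity". It then adds, for behaviour-change interventions, that "accelerometers provide the most valid estimates of change in energy expenditure". At study end, C.6.a says: "Participants will again be given an Actigraph device to wear for seven days".

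**Questionnaire.** C.3.c.1 brings in the PPAQ to supplement the step counts and says it adds context and domain to what the two devices give. It also says the PPAQ was chosen because it assesses total activity and has detailed walking items. On recall in general, A.5 warns that "recall of walking presents numerous challenges".

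**The concern.** The protocol assigns two instruments to one construct, then fixes the analysis to the one that depends on recall. The other is collected at both ends of the study, is rated more highly by the protocol's own text, and has no analysis attached.

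The choice matters here because of what the arms are. Participants are told to walk for 30 or 60 minutes, set goals, keep logs, attend group sessions and take weekly calls (C.5.a, C.5.b). They must know their target, and no masking to dose is described. Someone who has worked towards 60 minutes for twelve weeks may report more than someone who has worked towards 30, even if the two did the same. That would push the questionnaire comparison towards Hypothesis 2, which expects more activity in the 60-minute arm.

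At stake is the reading of the only planned measure of total activity beyond steps. A difference on the PPAQ could be activity, reporting, or both, and the plan states no objective comparison of minutes or intensity to set beside it.

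**Working it through.** No arithmetic decides this point. It turns on which instrument feeds which analysis, so the check follows each instrument through the protocol.

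| Instrument | Stated purpose | When collected | Analysis named in C.11 |
|---|---|---|---|
| Blinded pedometer | Named secondary outcome (Specific Aims); steps | Seven days at baseline and at study end (C.3.a, C.6.a) | Change in steps per day between arms; percentage reaching 10,000 and 13,000 steps |
| Accelerometer | Total activity, minutes by intensity, MET-minutes per week, energy expenditure (C.3.a, C.3.a.2) | Same baseline period as the pedometer (C.3.a); seven days at study end (C.6.a); download also shown in Figure 2 | None |
| PPAQ | Supplement to step counts; total and leisure-time activity; context and domain (C.3.c.1) | Baseline and follow-up (Table 2) | Total activity, within and between arms |

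1. **Can a change score be formed from the accelerometer?** Yes. It is worn at baseline and at study end by all participants.
2. **Is the construct the same?** Yes. C.3.a gives the accelerometer total physical activity, and C.11.b analyses total physical activity.
3. **Is the device used under another name?** Two items in C.11.b name no instrument: overall activity level as a predictor of meeting the step goal, and adherence defined as 90% of required activity. Either could draw on the accelerometer, but the text does not say so. Neither is a comparison of change in total activity between arms.
4. **Does the wear rule carry over?** No. The eight-hour minimum in C.11.b is written for pedometer days only. An accelerometer analysis would need its own rule.
5. **What does the pedometer already cover?** C.5.b defines the arms in steps as well as minutes: 13,000 − 10,000 = 3,000 steps per day apart. A.5.a puts 30 minutes of walking at 3,000 to 4,000 steps. Step counts therefore speak directly to whether the arms separated. What has no named objective analysis is minutes and intensity.

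**The case against.** The strongest reply is that the activity hypothesis does not rest on self-report. The secondary outcome is step count on a sealed pedometer, which leads C.11.b and has a wear rule and a model. The PPAQ comparison comes last and is supplementary. Reporting bias cannot reach the pedometer result. This stands, and it limits the importance of the point. A reader might infer that the trial gives up its only objective evidence that the two doses differed; step counts and step-goal attainment show that it does not.

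Second, C.3.c.1 does present the PPAQ as a measure of total activity, so C.11.b uses it for a purpose the protocol states. This also stands. It would be wrong to say the questionnaire is used against its stated role. The fault is narrower: of two instruments given the same job, only the one more open to arm-related bias is analysed.

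Third, a statistical analysis plan that is not at hand might add the accelerometer. Silence in the protocol would then be no fault. But the protocol is not silent: it names the instrument for this comparison.

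Two further readings go beyond the text. One is that the protocol calls accelerometry the gold standard for change. It does not: that label is attached to objective measurement, and the remark about change concerns energy expenditure. The other is to put a figure on the bias. If participants over-reported by 10% to 30% of their prescribed minutes, the gap between arms with no true difference would be 0.10 × (60 − 30) = 3 to 0.30 × (60 − 30) = 9 minutes per day, or 21 to 63 minutes per week. The protocol gives no over-reporting rate, and making the error proportional to the prescription builds the gap in. The figure repeats its assumption and is not evidence of size.

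**Conclusion.** The point holds in limited form. C.11.b fixes the supplementary total-activity comparison to the PPAQ alone, although accelerometry is collected at both visits for that construct and is rated by the protocol as the more valid measure of change in energy expenditure. The severity is low to moderate: neither the biomarker outcomes nor the pedometer outcome is affected, and the study describes itself as a pilot for feasibility.

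The conclusion rests on two assumptions. One is that participants know their assigned dose, which follows from the design although the protocol does not say so in terms. The other is that knowing it can influence what they report. The direction of the possible bias is towards Hypothesis 2; its size is unknown. Accelerometry does not remove every problem, since people may be more active while they know they are monitored, a risk the protocol recognises when it blinds the pedometers. It does remove the dependence on recall and reporting.

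**What to change.** In C.11.b, name accelerometer MET-minutes per week and minutes of moderate-to-vigorous activity, both already listed in C.3.a.2, as the main measure of total physical activity. Analyse change between arms with the same baseline-adjusted mixed model as the step counts. State an accelerometer wear-time rule: the minimum hours for a valid day and the minimum number of valid days. Keep the PPAQ comparison, labelled as supportive and used to describe the domains in which activity changed. State which instrument supplies the overall activity level used as a predictor in the same section.

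No new visit, device or participant burden is needed. The cost is a sentence or two of protocol text, a wear-time rule, some processing and analysis work, and the possible loss of participants with too little wear, which is noticeable with 10 per arm. The number excluded for that reason would itself be a useful feasibility result.

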Secondary Outcome: Change in physical activity level as measured by blinded pedometer.

The specific aims are:

**Primary Aim:** To conduct a dose response pilot trial of low (30 min/day) or high (60 min/day) dose exercise in men and women at increased risk of colon cancer. The major outcomes are changes in serum levels of four risk-related biomarkers: insulin, C-peptide, IL-6 and PGE-2.

Hypothesis 1: Exercise will decrease serum markers in a dose response manner.

**Secondary Aim.** To compare changes in the secondary outcome of physical activity over three months.

Hypothesis 2: Participants in the 60 minute intervention will have significantly higher physical activity levels than those in the 30 minute intervention at three months.

1. **RESEARCH DESIGN AND METHODS**

**C.1. Overview of research design and study.** The overall objective of this study is to compare two doses of physical activity delivered through existing walking intervention paradigm in 20 individuals at increased risk for colon cancer and evaluate the dose of activity necessary to change colon cancer risk related serum biomarkers. This 12-week two-arm randomized controlled trial will administer the First Plus walking program prescribing two different doses (30 minutes vs 60 minutes) of physical activity.^111, 112^ This study builds on previous physical activity interventions with cancer outcomes where 12 week interventions are common.^113-118^ The subjects in the study will be recruited from the gastroenterology practice at Barnes Jewish Hospital / Washington University School of Medicine (BJH/WUSM). The gastroenterology practice sees approximately 4000 patients per year for colonoscopy. Of these, half present for screening or surveillance procedures and approximately 20% of these present with adenomatous polyps. The patients are representative of the larger patient population at BJH/WUSM, with half being female and one third African American. Children are not screened for colon cancer and are thus not included in this study. The study will be coordinated and intervention delivered by [name], MS, RD, LD and overseen by [name]. [name] has a master’s degree in exercise physiology and extensive experience managing health promotion research studies. [name] will assist with data collection and management under [name] supervision. A study schema (Figure 2) is provided below.

Eligibility screening

Blinded pedometer protocol & accelerometer protocol (n=20)

Baseline assessment

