**C.3.c.1. Self-reported physical activity.** As a supplement to the step count data, participants will complete a physical activity questionnaire. We will use the Paffenbarger Physical Activity Questionnaire (PPAQ) which assesses moderate and vigorous intensity physical activity with distinct items to measure walking.^95, 122^ The PPAQ also allows measurement of both leisure time only and total (leisure time plus occupational and transport) physical activity. This validated instrument was selected because it provides an assessment of total physical activity while also employing several detailed walking items. The information in the PPAQ supplements that provided by the accelerometer and pedometer by providing information about context/domain of physical activity.

**C.3.c.2. Modifying mechanisms.** We will also collect information related to the intervention constructs using validated published scales whenever possible. Self-efficacy for physical activity will be measured using the Exercise Confidence Survey.^123^ Social support for physical activity will be measured using the Sallis Social Support Scale.^124^

| **Table 2. Survey measures** | | |  |  |
| --- | --- | --- | --- | --- |
| **Construct** | **Measure** | **Baseline** | | **Follow up** |
| Self-reported physical activity | Paffenbarger Questionnaire | X | | x |
| Sociodemographic | Age | X | |  |
|  | Marital Status | x | |  |
|  | Race/ethnicity | X | |  |
|  | Gender | X | |  |
|  | Education | X | |  |
|  | Income | X | |  |
|  | Occupation | X | |  |
|  | Immigrant status | X | |  |
| Other cancer risk factors | Family history of colorectal cancer | X | | x |
|  | Current and past tobacco use | X | | x |
|  | Hormone use (women only) | X | | x |
|  | Diet (Willett Questionnaire) | X | | x |
| Self efficacy | Exercise Confidence Survey | X | | x |
| Social support | Sallis Social Support Scale | X | | x |
| Neighborhood safety | Day/Night; Home/work | X | | x |
| Benefits of physical activity | HINTS questions | X | | x |
| Neighborhood walkability and access | IPAPS self administered module | X | | X |
| Length of residence |  | X | |  |
| Perceived neighborhood disorder |  | X | | X |
| Depression | CES-D | X | | X |
| Perceived Stress |  | X | | X |
| Coping strategies | Brief COPE | X | | X |
| Urban life stress | Urban Life Stress Scale | X | | X |

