Thus, based on our estimates, we estimate that 20 subjects per group is sufficient to detect differences in several of our outcomes, but not all. 50 subjects per group will provide sufficient power to detect differences in all our markers. However, as this is a pilot project we are not concerned with obtaining sufficient power in our outcomes and we will enroll 20 subjects (10 per group). We realize that participant drop out may prohibit our ability to detect differences in some outcomes, but as noted above, **this is a pilot feasibility study**.

**C.11. Data analysis**.

**C.11.a. Primary Aim:** To conduct a dose response pilot trial of low (30 min/day) or high (60 min/day) dose exercise in men and women at increased risk of colon cancer. The major outcomes are changes in serum levels of four risk-related biomarkers: insulin, C-peptide, IL-6 and PGE-2.

Hypothesis 1.1: First we will evaluate randomization success by comparing the two intervention groups on demographic and health factors. We will then evaluate intervention effects by differences in biomarker levels at study end between intervention groups using linear regression. We will compare differences in mean change in each of the biomarkers from baseline to three months between intervention groups. The analysis is based on change over three months using mixed effects regression models with PROC MIXED of SAS. The model is:

Y_it_ = α + β_1_t + β_2_X_i1_ + β_3_X_i1_t + β_4_tY_i0_ + e_it_

where Y_it_ = biomarker for subject i at time t, where t = 0 for baseline, t = 1 for 3 months.

X_i1_ = 1 if i^th^ subject is in the Plus intervention group, = 0 otherwise; e_it_ ~ N(0, σ^2^)

Of primary interest is β_3_ = mean difference in biomarker level change between intervention groups. The coefficient β_2_ allows for mean differences in level between groups at baseline. The coefficient β_4_ allows the change in biomarker to depend on initial level. We will conduct unadjusted analyses because of the randomization design but will also examine the effects of adjusting for sociodemographic factors, and family history of colon cancer. We will conduct outcome analyses based on assigned treatment at randomization regardless of adherence (intent to treat analysis). Throughout our analyses missing data will be imputed.^139^

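### Minor: C.11.b compares the arms on change in PPAQ total activity and states no baseline term; adjusting for baseline PPAQ would usually be more precise at almost no cost

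*Protocol*

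**What the plan says.** The last sentence of C.11.b has two parts. The first looks within groups, "comparing baseline and follow-up total physical activity levels (as measured by the PPAQ) in the intervention groups". The second compares the arms, "comparing change in those levels between the intervention groups using the general estimating equation modification to linear regression". No equation or covariate list is given for either part, and neither is tied to the model written out for Aim 1.

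The other longitudinal comparisons are specified differently. The biomarker model in C.11.a has a term in the baseline value, of which it says "The coefficient β_4_ allows the change in biomarker to depend on initial level". The effect of interest there is β3, the "mean difference in biomarker level change between intervention groups". C.11.b says that the step-count model follows the Aim 1 form.

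On the standing of PPAQ, C.3.c.1 introduces it with "As a supplement to the step count data, participants will complete a physical activity questionnaire". The Specific Aims name a different measure: "Secondary Outcome: Change in physical activity level as measured by blinded pedometer". Table 2 schedules PPAQ at baseline and follow-up. C.9 sets the trial at 10 per arm and says that power is not a concern in a pilot.

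**The concern.** A comparison of raw change subtracts the whole of each person's baseline value. Unless baseline and follow-up are very highly correlated, that removes too much. Baseline noise enters the estimate, and the arm that happened to report less activity at baseline is favoured. With 10 per arm such chance differences are not small. Regressing the follow-up value on arm and baseline estimates how much baseline to remove instead of fixing it at one.

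At stake is the width of the interval on one supplementary comparison, and how far a chance imbalance moves the observed result. Neither type I error nor the primary biomarker analysis is affected.

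**Working it through.** **Inputs.** 10 per arm (C.9). No PPAQ SD, correlation ρ or effect size is given, so ρ from 0.3 to 0.9 and a true difference of 1 SD are assumptions. Equal SDs at baseline and follow-up are assumed first and relaxed in step 5.

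**Plan's own figures.** There is none for PPAQ. C.9 uses the raw-change variance 2σ²(1−ρ) for the biomarkers. For insulin, 2 × 0.59² × 0.5 = 0.348, and 2 × 0.348 × (2.24 + 1.035)² / 1.1² = 6.17, against the stated 6. The change-score formula therefore reproduces the plan's result. (The variance of 123.63 printed in C.9 does not, but that is a separate matter.)

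**1. What the stated method estimates.** A GEE with arm, time and arm-by-time, fitted to two visits of simulated data, gave an arm-by-time coefficient of 1.1127. The difference in mean raw change was also 1.1127.

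**2. Precision at 10 per arm.** In units of σ² × 2/10:
- raw change: 2(1−ρ)
- baseline-adjusted: (1−ρ²) × (1 + 1/16), where the factor 17/16 is the small-sample cost of estimating the baseline slope.

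| ρ (assumed) | raw change | adjusted | ratio | variance saved |
|---|---|---|---|---|
| 0.3 | 1.40 | 0.967 | 0.69 | 31% |
| 0.5 | 1.00 | 0.797 | 0.80 | 20% |
| 0.7 | 0.60 | 0.542 | 0.90 | 10% |
| 0.85 | 0.30 | 0.295 | 0.98 | 2% |
| 0.9 | 0.20 | 0.202 | 1.01 | −1% |

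Break-even is where (1+ρ) × 17/16 = 2, so ρ = 15/17 = 0.88. Simulated variance ratios were 0.69, 0.80, 0.89 and 1.01 at ρ = 0.3, 0.5, 0.7 and 0.9.

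**3. Power.** Simulated for a 1-SD difference at two-sided 5%, raw change against adjusted: 43% and about 58% at ρ = 0.3; 56% and about 66% at 0.5; 78% and 82% at 0.7. Type I error was about 5% for both methods.

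**4. Chance imbalance.** The baseline difference between arms has SD √(2/10) = 0.45 SD. Raw change moves by −(1−ρ) per unit of that difference (simulated: −0.71, −0.51 and −0.31 at ρ = 0.3, 0.5 and 0.7). The adjusted estimate moves by about zero. At ρ = 0.5 a typical imbalance shifts raw change by 0.5 × 0.45 = 0.22 SD.

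**5. Unequal SDs.** The eligibility rules admit only people below an activity threshold, so the baseline SD may be smaller. If it is k times the follow-up SD, the raw-change variance becomes 1 + k² − 2ρk. At k = 0.5 and ρ = 0.5 this is 0.75 against 0.797 adjusted, so raw change is slightly better. With k of 0.75 or 0.5 and ρ of 0.3 to 0.7, simulated power ranged from 3 points worse with adjustment (65% against 68%) to 5 points better.

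**6. Is the Aim 1 model the remedy?** Let D0 and D1 be the arm differences at baseline and follow-up, and b the baseline slope. As written in C.11.a, with independent errors and an arm main effect, the baseline rows fix β2 = D0 and the follow-up rows give β2 + β3 = D1 − b·D0. Hence β3 = D1 − (1+b)·D0, with variance factor (1−ρ²) + 1 = 2 − ρ². At ρ = 0.5 that is 1.75, against 1.00 for raw change and 0.80 for the adjusted analysis. It also moves by about −1.0 per unit of baseline difference.

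**The case against.** The strongest objection is that the defect is read from silence. GEE regression can hold a baseline covariate, the sentence gives no covariate list, and such detail for a supplementary measure may be left to an analysis plan. This stands in part: the text does not exclude a baseline term. But it does name both the quantity compared and the technique. It also leaves out the link to the Aim 1 model that it makes for step counts. The plain reading is raw change, and it is fair to suggest a better analysis.

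Four stronger readings are tempting, and the Protocol does not support them.

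- A reader might infer that raw change is always the noisier choice. At this sample size that fails above a correlation of about 0.88, or when the baseline SD is well below the follow-up SD.
- A reader might take the remark in A.5 that "recall of walking presents numerous challenges" as evidence of a low PPAQ correlation. That passage argues for objective devices. It gives no repeat correlation, and C.3.c.1 describes the PPAQ as validated.
- A reader might hold up the biomarker and step-count models as the sound standard that PPAQ departs from. Step 6 shows that β3 as written is less precise than raw change and more sensitive to imbalance.
- A reader might conclude that the result is biased, or that the trial cannot afford the loss. Raw change is unbiased over randomisations, and the imbalance effect is conditional on the draw. PPAQ is supplementary, and the pilot disclaims power.

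The two-visit premise is also not secure. The Specific Aims mention outcomes at one month, and the schema's Phase I assessment repeats the baseline battery apart from sociodemographic and risk-factor items, which would include PPAQ. C.6 and C.11.b point to baseline and study end only. The fix has to allow for both.

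**Conclusion.** The point holds as a minor, nearly free improvement. The PPAQ comparison in C.11.b, as stated, is valid but usually less precise than an analysis adjusted for baseline PPAQ, and it lets chance baseline differences into the observed estimate. With 10 per arm and equal SDs, adjustment saves about 31%, 20% or 10% of the variance at correlations of 0.3, 0.5 or 0.7. It saves nothing near 0.88. If the baseline SD is well below the follow-up SD, it can lose about 3 power points. All of these sizes rest on assumed correlations and SDs, and the power figures also on an assumed 1-SD effect. That the pilot is not concerned with power explains the sample size; it is no reason to prefer the less efficient analysis of data already collected.

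**What to change.** In C.11.b, replace the between-arm part of the last sentence with a linear regression of three-month PPAQ total activity on arm, with baseline PPAQ total activity as covariate. Use a t reference (20 − 3 = 17 residual degrees of freedom with complete data), and report the arm coefficient with its 95% CI. The within-group description can stay.

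State whether PPAQ is collected at the Phase I assessment. If it is, keep that visit as a further follow-up outcome in a repeated-measures model with baseline PPAQ as covariate, so that its data are not discarded, and report the three-month arm difference from that model.

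Do not carry the C.11.a equation over to PPAQ, for the reason in step 6 of the working.

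The cost is one or two sentences and one degree of freedom. No new data or participants are needed, and under randomisation the quantity estimated is the same.
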